## Abstract

**Background:**

Inadequate diets and life-threatening infections have profound adverse implications for child growth, development, and survival, particularly among indigenous peoples. Evidence of the effectiveness of community-based nutrition education interventions in improving child feeding and nutrition outcomes among indigenous Mbororo population in Cameroon is scarce.

**Objective:**

This study aims to investigate the impact of culturally tailored community-based nutrition education intervention on caregivers’ knowledge, attitude, and practice regarding complementary feeding and on nutrition outcomes of indigenous Mbororo children (aged 3-59 months) in the Foumban and Galim health districts of the West Region of Cameroon.

**Methods:**

A two-arm cluster randomized controlled trial will be conducted in the Foumban Health District and Galim Health District. The intervention and control arms will each comprise 5 clusters with 121 child–caregiver pairs. Participants in the intervention arm will be organized into 5 caregivers’ peer-support platforms. A total of 12 educational sessions will be assigned to the intervention group by trained female Mbororo nutrition volunteers (n=6) and community health workers (n=6). The control arm will receive routine facility-based nutrition education. Data will be collected at 3-month and 6-month follow-up. Both descriptive statistics and multivariate logistic models will be used to estimate the effect of culturally tailored community-based nutrition education intervention (independent variable) on outcome variables (caregivers’ knowledge, attitude, and practice), child growth (weight, height/length, weight for age), and morbidity status (diarrhea, cough, and fever) between both arms. Data assessors will be blinded to the group allocation. Ethical approval (reference no. 2019/1002-07/UB/SG/IRB/FHS) was obtained from the Faculty of Health Sciences Institutional Review Board at the University of Buea.

**Results:**

Baseline data were collected in September 2019. In February 2020, 10 Mbororo communities (clusters) with 242 child–caregiver pairs were selected and allocated to the experimental and control arm in a 1:1 ratio. Community nutrition volunteers (n=6) and community health workers (n=6) were selected and trained. Data collection and analysis are ongoing, and results are not available for this manuscript.

**Conclusions:**

The findings of this study will provide evidence on the impact of culturally tailored and health belief model–based nutrition education on behavior change as a complementary strategy for strengthening health facility–based approaches in the reduction of malnutrition burden among the study population

**International Registered Report Identifier (IRRID):**

DERR1-10.2196/23115

## Introduction

Every year, 5.6 million children die before their fifth birthday, with 80% of these deaths occurring in sub-Saharan Africa and Asia [1]. Malnutrition accounts for more than 45% of all child deaths globally [2]. Thus, achieving the Sustainable Development Goal Target 2.2 [3] of ending all forms of malnutrition will significantly contribute to the reduction of child mortality to 25 deaths per 1000 live births in every country by 2030 [3]. Effective malnutrition reduction strategies hinge largely on reducing key underlying factors, particularly among those groups identified as high-risk according to evidence-based approaches [4].

Poor diets and life-threatening infections during childhood, such as diarrhea and pneumonia, are the immediate and major causes of childhood undernutrition in developing countries [1,5]. Low maternal socioeconomic status, inadequate nutrition capacity, limited access to health care, and poverty are important contributing factors [1]. In particular, inadequate maternal knowledge regarding exclusive breastfeeding and complementary feeding practices has been implicated in childhood undernutrition [5,6]. In Cameroon, more than half of children aged 6-23 months do not receive adequate complementary feeding, and only 33% of these children receive the minimum dietary diversity [7]. Improving mothers’/caregivers’ child-feeding behavior is thus an important target and has the potential to improve child nutritional status and survival.

Community‐based programs are unique platforms for the delivery of nutrition interventions [8]. Pooled analyses show that home-based and community-based nutrition education interventions for mothers improve the nutritional status of children younger than 5 years in developing countries [9,10]. Similarly, hygiene counseling components of interventions significantly decrease diarrhea episodes and dysentery among children younger than 5 years [11]. Intervention delivery strategies, such as home visiting, conducting group meetings of caregivers and community leaders, providing education regularly, and the use of cooking demonstrations, have been shown to produce positive outcomes [9].

In Cameroon, the nutrition education for mothers is predominantly facility based. Within the context of a weak health care system, characterized by low coverage, underresourcing, and workforce shortage [12], community-based strategies are needed to complement and strengthen facility-based approaches. Further, facility-based education often fails to adequately address context-specific barriers to behavior change. Moreover, the potential for community-based nutrition education targeting the Mbororo population in Cameroon has not been adequately explored. As an ethnic minority indigenous people [13], the Mbororo reside predominantly in hard-to-reach rural settings where child malnutrition rates are disproportionately higher [7]. It is worth nothing that indigenous children experience higher nutrition-related problems than their nonindigenous counterparts worldwide [14,15]. It is against this background that this study is designed to evaluate the effect of a nutrition education intervention on caregivers’ nutrition-related knowledge, attitude, and practice (KAP) and nutrition outcomes of indigenous Mbororo children younger than 5 years in the study area. The study design is informed by the health belief model and contextual realities of the target community obtained from the formative study. The study is innovative and culturally tailored to ensure acceptability and sustainability. The findings will contribute to the growing body of evidence on community-based nutrition education for behavior change as a complementary strategy for strengthening health care systems and achieving overall child health–related goals in Cameroon.

## Methods

### Trial Registration Status

The protocol was submitted to the Wealth Health Organization (WHO) Pan Africa Clinical Trial Registry in South Africa for review. Feedback is still being awaited. The last correspondence was on July 4, 2020.

### Trial Design

As presented in Figure 1, this is a 2-arm parallel intervention study designed as a cluster randomized controlled trial. The randomization units will be clusters to prevent contamination between the experimental and control arms. A computer-generated list of 10 randomly selected clusters will be produced and placed in sealed, opaque envelopes.

**Figure 1 figure1:**
[figure not shown]
Flow chart showing cluster randomization and follow-up for the nutrition, water, sanitation, and hygiene (Nu-Wash) model.

The clusters will be allocated in a 1:1 ratio in both arms. The study will be single blinded, as only the data assessors (data collectors and analysts) will be blinded to the group allocations. Within each cluster, children and caregivers meeting the inclusion criteria will be recruited for the study. Informed consent and assent will be obtained from caregivers before the intervention. Caregivers in the experimental arm will receive nutritional education under the nutrition, water, sanitation, and hygiene (Nu-WASH) model, and caregivers in the control arm will be exposed to routine nutrition education offered by health staff in the study area. Data will be collected at 3-month and 6-month follow-up.

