### Study Participants: Inclusion and Exclusion Criteria

The study will comprise Mbororo children and their primary caregivers selected from 10 participating Mbororo communities in the Foumban Health District and Galim Health District. Participants enrolled in the study will include Mbororo households with child–caregiver pairs who participated at baseline data collection and who meet the following inclusion criteria: the children should be between 3 and 59 months of age, while their female primary caregivers should have 6 months minimum residence status, no intention to leave before the end of the study, and have provided their verbal or written informed consent and assent to participate in the study. Mbororo households without children younger than 5 years, those who did not participate at baseline data collection, those without permanent residence, children and caregivers who become seriously sick, and caregivers who refuse to participate in the study will be excluded.

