### Data Analysis Plan

Like the procedure at baseline, 1 biostatistician and 2 trained data entry clerks will be responsible for the endline data management and analysis. Data will be cross-checked for inconsistencies (outliers and extreme points) and errors and incompleteness before, during, and after manual entry into SPSS version 23 (IBM Corp). The data will be further treated for reverse coding, potential points, and outliers, as well as missing data, before being exported to SmartPLS2 for further investigation and fitting of the structural model.

Sociodemographic and child morbidity data will be analyzed and summarized using descriptive statistics. The data will be expressed as mean (SD) or median (range) for continuous variables and as a number (percentages) for categorical variables. The *t* test and analysis of variance for comparing group means will be used for primary and secondary outcome variables. A chi-square test will be applied to analyze the categorized variables. Child nutrition outcomes will be computed from anthropometric indices using Stata version 11 (StataCorp) and compared with the WHO 2006 growth standard median [20].

Results for group comparisons will be expressed as a risk ratio for binary outcomes, corresponding to 2-sided 95% CIs, and associated *P* values. *P* values will be adjusted to 2 decimal places with values less than .01 reported as <.01. Adjusted analyses using baseline variables will be performed using multivariate logistic regression to determine the continuing influence of key baseline characteristics on the outcomes. The Kaplan-Meier survival analysis will be used for timed variables like morbidity. Intention-to-treat analysis will be used, and the clustering effect will be considered in the analysis. All analyses will be performed at a 95% CI. The significance level will be set at a *P* value <.05.

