### Ethical Considerations

Ethical approval (reference no. 2019/1002-07/UB/SG/IRB/FHS) for the study was obtained from the Faculty of Health Sciences Institutional Review Board at the University of Buea. Administrative authorization was sought from the West Regional Delegation of Public Health. Informed verbal and signed consent and parental assent will be obtained from study participants before inclusion in the study. Participation will be voluntary with participants being able to withdraw from the study at any time. Anonymity and confidentiality will be assured and maintained.

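### Consent and several exclusions are not tied to a time before cluster allocation, so pairs could be lost by arm from the 242 already listed, against the declared intention-to-treat analysis

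*Protocol article*

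**What the plan says.** The paragraph after Figure 1 in Trial Design gives the steps in this order.

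- Allocation: "The clusters will be allocated in a 1:1 ratio in both arms".
- Blinding: "only the data assessors (data collectors and analysts) will be blinded to the group allocations".
- Recruitment: "Within each cluster, children and caregivers meeting the inclusion criteria will be recruited for the study".
- Consent: "Informed consent and assent will be obtained from caregivers before the intervention".

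Ethical Considerations says that consent "will be obtained from study participants before inclusion in the study", which again does not refer to allocation.

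Study Participants: Inclusion and Exclusion Criteria admits only pairs who took part in the baseline survey. It then sets further conditions on them. Caregivers must have "no intention to leave before the end of the study, and have provided their verbal or written informed consent", and "caregivers who refuse to participate in the study will be excluded". Children and caregivers who fall seriously ill are excluded as well. None of these conditions carries a date.

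The Data Analysis Plan states "Intention-to-treat analysis will be used" and does not define the set.

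**The concern.** Randomising communities protects the comparison only if membership of each community's sample is settled without regard to the arm. In this trial the two offers differ greatly. Step 4 gives the intervention arm 12 fortnightly sessions of 90 to 120 minutes, which is 18 to 24 hours per caregiver over six months (12 × 90 = 1,080 minutes; 12 × 120 = 1,440 minutes). The control arm has routine facility-based education. A caregiver who knows her arm may have different reasons to refuse, or to say that she plans to move.

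Serious illness raises a separate problem. It is related to the secondary outcomes of diarrhoea, fever and cough, so removing pairs for illness after allocation would select on something close to the outcome.

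The primary outcomes are self-reported knowledge, attitude and practice scores, on which selection by motivation could act directly. An intention-to-treat analysis cannot recover pairs that have been ruled ineligible and never enter the set.

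**Working it through.** **1. Dates.** Baseline data were collected in August to September 2019 (Step 1; Results). Communities and pairs were selected and allocated in February 2020 (Abstract, Results), about five months later. Consent, the final eligibility check and the opening of the envelopes have no dates.

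**2. Counts.** Step 1 gives 242 pairs in 10 communities. The Abstract gives 121 pairs per arm, and 2 × 121 = 242. Step 2 reports 121 intervention caregivers already organised into groups. The counts agree, so no loss is visible up to the formation of the groups. They do not say when consent was taken, or what happens to a listed pair afterwards.

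**3. What the baseline restriction does.** Only baseline participants are eligible, so nobody can be added after allocation. However, the eligibility section lists absence from baseline and refusal as separate exclusions. A baseline participant can therefore still be removed for refusing. The illness exclusion is worded as a change of state, which points to events after baseline.

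**4. Conflict with intention to treat.** If a listed pair in an allocated community is removed after allocation for refusal, planned departure or illness, the analysed set is no longer the allocated set. The exclusion rule has no time limit, so it permits this; the Data Analysis Plan says the opposite.

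**5. Size, on assumed values.** The documents give no losses by arm. The only related figure is the 10% non-response allowance in Sample Size Determination, which is not split by arm.

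Let r be the proportion lost in an arm, and D the difference between retained and lost caregivers, in SDs of the analysed score and the same in both arms. The overall mean is (1 − r) × retained + r × lost, so the retained mean exceeds the overall mean by r × D. The shift in the arm difference is therefore, in absolute value,

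|r(arm 1) − r(arm 2)| × D.

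| Loss in the two arms | D = 0.2 | D = 0.5 | D = 0.8 |
|---|---|---|---|
| 5% v 5% | 0 | 0 | 0 |
| 5% v 10% | 0.01 | 0.025 | 0.04 |
| 5% v 20% | 0.03 | 0.075 | 0.12 |

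For example, (0.20 − 0.05) × 0.8 = 0.12 SD. Of 121 pairs, 5%, 10% and 20% are about 6, 12 and 24. The zeros in the first row need D to be equal in the two arms; equal numbers lost for different reasons could still shift the difference.

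**6. Scale.** With 121 per arm and no allowance for clustering, the standard error of a difference in means is √(2/121) ≈ 0.13 SD. The largest entry is just below one such standard error.

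**The case against.** A reader might infer that eligibility, refusal and consent were in fact settled after allocation, with caregivers already aware of their arm. The documents do not support that. The Trial Design paragraph is an undated summary, and the order of its sentences is not proof of chronology. Consent before the intervention is only a latest limit, and is compatible with consent before the envelopes were opened. The envelopes are described as sealed and opaque, and no text says when communities learned their arm. The dated text shows 242 pairs identified by the time of allocation. Figure 1 might show the order but is not available here.

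A reader might also infer that the plan drops caregivers who skip sessions, and so favours Nu-WASH. That goes too far. The exclusion is for refusing the study, Step 5 monitors compliance without removing non-compliers, and Ethical Considerations treats later withdrawal separately. The direction of any bias is not established either. Table 1 analyses change scores, which remove whatever part of the difference was present at baseline, and low scorers may have more room to improve.

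The size is assumed and modest, as steps 5 and 6 show. These objections limit the point and lower its severity.

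It can also be said that an article leaves consent dates and the definition of the analysis set to a fuller document. That holds for the dates alone. It does not answer the remaining point: the article states exclusion rules without a time limit beside a declared intention-to-treat analysis, and the two conflict if the rules are applied after allocation.

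**Conclusion.** The point holds in a limited form. The article places recruitment and consent after allocation in its description, ties consent only to the intervention, and applies undated exclusions to pairs already identified in 2019. It does not show that these steps were complete by February 2020. If they were applied later, they allow arm-dependent loss from the 242 pairs and contradict the declared analysis. New households cannot enter.

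The shift of about 0.01 to 0.12 SD rests wholly on the assumed losses and on assumed differences between retained and lost caregivers; it is zero if losses and their reasons are equal by arm. It is a systematic shift, so a larger sample would not remove it. The point falls below a must-fix, but it deserves correction because the article reports that no results are yet available and the set can still be fixed before arms are compared.

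**What to change.** 1. Define the intention-to-treat set as all 242 pairs selected for the trial from the baseline participants, analysed by the arm of their allocated community. The set should be these 242 pairs and not everyone surveyed at baseline, because the article does not say whether the survey was larger.
2. For analysis, count refusal of sessions, a plan to leave or serious illness arising after allocation as non-adherence or missing follow-up, and not as ineligibility. This concerns the analysis set only and leaves clinical decisions untouched.
3. Seek the 3-month and 6-month survey from those pairs where the caregiver agrees to be surveyed.
4. State the actual dates of consent, final eligibility and envelope opening, without asserting an order that did not occur. If consent came before allocation, one sentence settles that part; the undated exclusions still need a time limit.
5. Report losses from the 242 pairs by arm, cluster and reason, with the baseline data of those lost.

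The cost is a change of wording, use of a list already held, a few extra follow-up visits to caregivers who do not attend, and a slightly diluted effect estimate.

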### Trial Setting

The study will be conducted in the West Region of Cameron with an estimated population of 1,785,285 inhabitants and a surface area of 13,960 km^2^ [16]. The population is largely rural and relies on agro- and commercial businesses for livelihoods and income. The region is host to several cultural groupings, including the indigenous Mbororo peoples, who reside in larger communities in the Bangouraim, Bangante, Foumban, Foumbot, Kouoptamo, Galim, and Mbouda health districts of the region. Foumban Health District and Galim Health District were randomly selected for the study.

### Study Participants: Inclusion and Exclusion Criteria

The study will comprise Mbororo children and their primary caregivers selected from 10 participating Mbororo communities in the Foumban Health District and Galim Health District. Participants enrolled in the study will include Mbororo households with child–caregiver pairs who participated at baseline data collection and who meet the following inclusion criteria: the children should be between 3 and 59 months of age, while their female primary caregivers should have 6 months minimum residence status, no intention to leave before the end of the study, and have provided their verbal or written informed consent and assent to participate in the study. Mbororo households without children younger than 5 years, those who did not participate at baseline data collection, those without permanent residence, children and caregivers who become seriously sick, and caregivers who refuse to participate in the study will be excluded.

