### Intervention

Our Nu-WASH model comprises nutrition, and water, sanitation, and hygiene components. The nutrition component includes the following: complementary feeding, which involves the nutrition needs for young children; benefits of continuous breastfeeding for up to 24 months of child age; nutritional value of locally available plant-based and animal-based food items; dietary diversity (nutrient-rich homemade recipes); benefits and challenges of adequate complementary feeding practices; and susceptibility to, and severity of, child undernutrition. The WASH component, aimed at improving caregivers’ WASH knowledge and practices, will include the following: WASH-related childhood diseases, including causes, susceptibility, and severity; water quality, including point-of-use household drinking water treatment (boiling and filtration), and safe storage; environmental sanitation, including safe collection of child feces; personal hygiene, including proper hand washing with soap before food preparation, before child feeding, after using the toilet, after disposing of garbage, and after cleaning the baby’s feces; food hygiene (preparation, covering, serving, and heating); and the perceived barriers and benefits of food hygiene.

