### Study Objectives

#### Primary Objective

The primary objective will be to investigate the impact of a Nu-WASH versus facility-based nutrition education on caregivers’ KAP regarding complementary feeding at baseline, 3-month follow-up, and 6-month follow-up. In the absence of a gold standard test in the measurement of KAP, composite measures will be used in this study. A composite knowledge score will be built on 4 measures based on 4 self-report questionnaire items. Knowledge will first be estimated by each measure and classified into 2 categories as adequate and inadequate before the results of the 4 measures are finally combined into the composite knowledge score. Similarly, composite scores for attitude and practice will comprise 10 and 7 measures, respectively, as derived from corresponding numbers of self-report questionnaire items.

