**Primary Outcomes**														
	Caregivers’ knowledge			Ratio			Continuous			Change in knowledge scores			*t* test	
	Caregivers’ attitudes			Ratio			Continuous			Change in attitudes scores			*t* test	
	Caregivers’ practices			Ratio			Continuous			Change in practices scores			*t* test	

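### The primary practice score concerns complementary feeding, yet it is compared over children aged 3-59 months with no stated use of the child's age

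*Protocol article*

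**What the plan says.** All references are to the protocol article.

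- **Eligibility** (Study Participants): "the children should be between 3 and 59 months of age".
- **Primary objective:** to compare the arms on "caregivers’ KAP regarding complementary feeding at baseline, 3-month follow-up, and 6-month follow-up".
- **Practice score** (Primary Objective): "composite scores for attitude and practice will comprise 10 and 7 measures, respectively". The seven practice items are self-reported and their wording is not shown.
- **Primary measure** (Table 1): "Change in practices scores", treated as continuous and compared by t test over all pairs.
- **Age band for complementary feeding:** given once, as national background in the Introduction: "more than half of children aged 6-23 months do not receive adequate complementary feeding". The taught content also refers to the "benefits of continuous breastfeeding for up to 24 months of child age" (Intervention).
- **Adjustment** (Data Analysis Plan): adjusted analyses on baseline variables are planned by multivariate logistic regression. The covariates are not named. Clustering is to be taken into account.
- **Dates** (Abstract, Results): "Baseline data were collected in September 2019"; clusters were allocated in February 2020. Follow-up is at 3 and 6 months, and the start of that clock is not stated.

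**The concern.** Knowledge and attitude can be asked of any caregiver. What a caregiver currently feeds a child depends on the child's age. Complementary feeding belongs to a limited age range, and the eligible range is about three times as wide as the one band that the article mentions. A single practice score over all pairs therefore combines caregivers whose child is at the stage in question with caregivers whose child is past it or, at baseline, not yet in it.

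Three things are at stake for one of the three primary outcomes:

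- Unexplained variation by age lowers precision.
- With 5 clusters per arm, the arms may differ in age by chance, and a t test on the change score does not correct for this.
- If older children's feeding responds less, the all-age difference understates the effect on complementary feeding, and a conclusion worded for complementary feeding would rest partly on children past that stage.

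**Working it through.** The plan gives no figure on this point to reproduce, so the check is how many children could fall in the 6-23-month band and what follows.

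**Inputs from the article:** ages 3-59 months, which is 57 completed months; band 6-23 months, which is 18 months; 121 pairs and 5 clusters per arm, 242 pairs in all. September 2019 to February 2020 is about 5 months, so the 6-month visit falls about 11 months after baseline if follow-up runs from allocation, or 6 months after if it runs from baseline.

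**Assumptions, not in the article:** uniform baseline ages, with a younger-skewed alternative (density three times higher at 3 than at 59 months); intracluster correlation (ICC) 0.01 to 0.10.

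**1. Share of children aged 6-23 months**

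| | Baseline ages that qualify | Uniform | Skewed young |
|---|---|---|---|
| At baseline | 6-23 | 18/57 = 32% | 41% |
| At 6-month visit, 11-month gap | 3-12 | 10/57 = 18% | 25% |
| At both, 11-month gap | 6-12 | 7/57 = 12% | 17% |
| At 6-month visit, 6-month gap | 3-17 | 15/57 = 26% | not needed |
| At both, 6-month gap | 6-17 | 12/57 = 21% | not needed |

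If ages ran uniformly only from 3 to under 36 months, 18/33 = 55% would be in the band at baseline and 10/33 = 30% at the 11-month point.

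**2. All-age effect relative to the in-band effect.** Let p be the share in the band at the 6-month visit and r the out-of-band effect as a fraction of the in-band effect. The ratio is p + (1 - p)r.

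- r = 0: 18% (p = 0.175) to 26% (p = 0.263).
- r = 0.5: 0.175 + 0.825 × 0.5 = 59%; 0.263 + 0.737 × 0.5 = 63%.
- r = 1: 100%, no understatement.

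**3. Cost of looking only at ages 6-23 months.** With n_r = 121p per arm, the ratio of standard errors is sqrt{[(1 + (n_r/5 - 1)ICC)/n_r] / [(1 + (121/5 - 1)ICC)/121]}.

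For p = 0.175, n_r = 21.2:

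- ICC 0.01: sqrt[(1.032/21.2)/(1.232/121)] = 2.19
- ICC 0.05: sqrt[(1.162/21.2)/(2.160/121)] = 1.75
- ICC 0.10: sqrt[(1.324/21.2)/(3.320/121)] = 1.51

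The restricted comparison has the larger effect-to-standard-error ratio only if r is below (1/ratio - 0.175)/0.825, which is 0.34, 0.48 and 0.59 respectively. It would rest on about 242 × 0.175 = 42 pairs, about 4 per cluster.

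**4. Size of a chance age imbalance.** If age is unrelated to cluster, the standard error of the between-arm difference in the in-band share is sqrt[2p(1 - p)/121]. That is sqrt(2 × 0.175 × 0.825/121) = 4.9 percentage points, or 5.7 points for p = 0.263. A one-standard-error imbalance shifts the unadjusted comparison by about 0.05 times the gap in score between in-band and other children. The shift is larger if ages cluster by community.

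**The case against.** The strongest reply is that the size of the problem rests on things not shown.

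- **The band is background.** The 6-23-month figure is a national statistic, not the definition of the outcome, and the Primary Outcomes section calls the outcomes nutrition-related, which is broader. This stands. The primary objective does name complementary feeding, however, and the Caregivers' Interviews section lists complementary feeding practices separately from water, sanitation and hygiene.
- **The seven items and the ages are unknown.** This stands. A reader might infer that items are scored as inadequate for children to whom they do not apply. No text says so, and item scoring is something an article may leave to fuller documents.
- **Older children can respond.** The taught content includes dietary diversity, food hygiene, handwashing and cooking demonstrations, much of which applies at 24-59 months. This stands, so the zero-response case in step 2 is an extreme and not an estimate.
- **Ageing between visits is common to both arms.** A reader might infer bias because children change feeding stage between baseline and endline. Under randomisation both arms age equally, so this adds noise and no systematic between-arm shift.
- **Adjusted analyses are already planned.** This does not settle the point. The named model is logistic, the covariates are unnamed, and the practice outcome is a continuous change score compared by t test.

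**Conclusion.** The point holds as a weakness in how the practice outcome is analysed. The objective concerns a practice tied to early childhood, the score pools ages 3-59 months, and no use of child age is stated for it. Under uniform ages, about 32% of children are aged 6-23 months at baseline and about 18-26% at the 6-month visit. Age is therefore likely to be a strong source of variation, a chance imbalance could move the unadjusted result, and the all-age effect may understate the effect on complementary feeding.

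Two stronger readings are not supported. One is that the effect is diluted to 18-26% of its true size; that needs zero response outside the band, and with half the response retained the figure is 59-63%. The other is that the 6-23-month children should supply the answer to the objective; the break-even of 0.34-0.59 (11-month reading) shows that this could lose as much as it gains.

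Knowledge and attitude are not affected in the same way.

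**What to change.** 1. Keep the all-age practice comparison as primary. Replace the unadjusted t test with a comparison adjusted for the child's age at the visit (under 6, 6-23, 24 months and over) and for baseline practice score, allowing for clustering. A child at least 3 months old at baseline is at least 6 months old by the 3-month visit, so the youngest group matters only for the baseline measurement.
2. Prespecify a supporting between-arm estimate of the follow-up practice score in children aged 6-23 months at that visit, and report it beside the all-age result.
3. Word the conclusion on complementary feeding in light of both estimates.

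The cost is analysis-plan wording and a little more analysis. Child demographics are already in the questionnaire, so no new data or participants are needed. The downside is a wide interval for the 6-23-month estimate: under uniform ages and the 11-month reading its standard error is about 1.5 (ICC 0.10) to 2.2 (ICC 0.01) times that of the all-age comparison. That is why it is proposed as supporting and not as primary.
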